### Inclusion and exclusion criteria

Inclusion criteria are 1) main diagnosis of MDD, single episode or recurrent, moderate or severe (Beck Depression Inventory-II (BDI-II) - score ≥ 20 [87] or Montgomery-Asberg Depression Ratings Scale (MADRS)-score ≥ 20 [88]), without psychotic symptoms representing ICD-10 diagnoses (F32.1, F32.2, F33.1, or F33.2, 2) age between 18 and 75 years, and 3) informed consent to the study procedures and assessments in written form.

Exclusion criteria are 1) diagnosis of MDD, single episode or recurrent, severe with psychotic symptoms (F32.3, F33.3 according to ICD-10), 2) acute suicidality, 3) lifetime history of any psychotic or bipolar disorder, 4) severe neurological or internal concomitant or past diseases, 5) an IQ < 80 and/or severe learning disability, 6) current alcohol or any illicit drug withdrawal syndrome, 7) concomitant organic mental disorder (F00 – F09 according to ICD 10), 8) concomitant substance induced disorders, 9) severe mutism or stupor, 10) mental disorder secondary to a medical condition or substance use disorders, 11) pregnancy and lactation period, and 12) missing eligibility for psychotherapy due to language barriers.

Drop-outs during the conduct of the study were defined as enrolled participants 1) who withdraw informed consent, 2) for whom exclusion criteria became known to be fulfilled during the conduct of the study (such as a bipolar-diagnosis in the previous medical history discovered during the trial), or 3) who missed more than six sessions of psychotherapy (corresponds to 22% of the overall psychotherapy dose). To sum up, we anticipate these criteria to result in a heterogeneous sample that corresponds to the clinical reality of a psychiatric hospital.

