For the analysis of primary and secondary outcome variables, we will apply linear mixed-effect models (e.g. to explore predictors) which outperform other approaches like analysis of covariance when data is missing not completely at random [191] . Additionally, linear mixed-effect models have increased power compared to simple linear regression approaches as the intra-class coefficient increases [192], thus, a targeted sample size of *N* = 300 is likely a conservative estimate to assess treatment effects with a power of 80% and an alpha level of 0.05. When investigating treatment outcome in clinical trials, the role of missing values needs to be considered. In order to deal with them adequately, we will follow an intention-to-treat approach using multiple imputation techniques [193] and use more specialized statistical analyses such as survival analyses e.g., to investigate dropout as a clinically relevant secondary outcome. For investigating specific and non-specific MOCs in ST, CBT, and IST treatment arm (H3 – H5), we will fit growth models within multilevel and structural equation model frameworks taking into account the nested structure of the data and potential meaningful growth over time [194, 195]. Multilevel models are able to differentiate within- from between-person variation considering the hierarchies within the data (such as time point of measurements within individuals) and by including random slopes and random intercepts [194, 196].

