### Data management and monitoring

Data collection and management is conducted according to German law. Here, patient data is stored on encrypted institute servers in pseudonymized manner to restrict access to full details (i.e., personal identifying and study data) to dedicated study personnel only. In order to ensure data quality, double data entry is applied. If requested by a participant, all individual data is removed from all servers immediately. Data presented in publications will be fully anonymous and will not allow identification of study participants. Study documents will be kept at the Max Planck Institute of Psychiatry for the duration of the study and consecutive data analysis. All data that is not kept in the biobank, will be deleted 25 years after end of the study.

The occurrence of adverse events, defined as the development of acute suicidality, and serious adverse events, defined as suicide attempt, will lead to the immediate exclusion of the participant from any study procedures. In such cases, necessary psychiatric care will be provided. Serious adverse events are reported to the Institutional Ethic Committee of the Faculty of Medicine of Ludwig-Maximilians-University Munich. If they are related to study procedures, the study is terminated immediately.

Since it is a psychotherapy trial, blinding of participants and personnel (except from raters) in the OPTIMA trial is impossible and potential adverse events or deteriorations directly assignable to treatment conditions. Therefore, the establishement of a data monitoring committee, which is normally installed in masked trials to supervise adverse events and potential relations to the experimental treatment condition, is not necessary.

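### Exclusion from all study procedures after acute suicidality or a suicide attempt, read literally, stops outcome measurement for a reason tied to the outcome

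*Protocol article*

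**What the plan says.** Three parts of the protocol article bear on this.

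- **Data management and monitoring.** The trigger is "The occurrence of adverse events, defined as the development of acute suicidality, and serious adverse events, defined as suicide attempt". Either event "will lead to the immediate exclusion of the participant from any study procedures". Nothing in this section, or elsewhere, keeps outcome assessment going afterwards.
- **Power and statistical analysis.** "For the analysis of primary and secondary outcome variables, we will apply linear mixed-effect models". On missing values, "we will follow an intention-to-treat approach using multiple imputation techniques". The Discussion lists intention-to-treat analysis among the methodological standards of the trial.
- **Inclusion and exclusion criteria.** "Drop-outs during the conduct of the study were defined as enrolled participants" in one of three groups: those "who withdraw informed consent", those "for whom exclusion criteria became known to be fulfilled during the conduct of the study", and those who missed more than six therapy sessions. The exclusion criteria include "2) acute suicidality, 3) lifetime history of any psychotic or bipolar disorder". Drop-out rate is a secondary outcome (Primary and secondary measures for outcome comparison), and survival analysis is planned for it.

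**The concern.** In a depression trial, acute suicidality or a suicide attempt usually signals deterioration. If measurement ends at that moment, the later scores are missing because of how the patient was doing. Intention-to-treat analysis depends on outcome data being sought for everyone randomised, whatever happens to their treatment. Here the investigators end the data collection themselves, so the missing values are avoidable.

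Standard multiple imputation and mixed models assume that unseen scores can be predicted from observed ones. If they cannot, the arm with more of these events looks better than it is. If that arm is schema therapy, the error favours both the superiority claim over supportive therapy (H1) and the non-inferiority claim against CBT (H2). If it is a comparator, the error works against schema therapy. Separately, a drop-out outcome cannot be compared between arms unless it is clear whether these exits count in it.

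**Working it through.** **1. The plan's own figures reproduce.** For H1 (d = 0.4, two-sided 0.05, power 0.80, t-test) n is 99.08 per group, against the stated 99.1. For H2 (n = 100 per group, one-sided 0.05, power 0.80) the detectable margin is 0.353. At the stated 0.36 the power is 0.814. Both serve below as yardsticks.

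**2. Does the rule cover outcome assessment?** Under Setting, recruitment and enrollment, the timeline of measures is listed among the study procedures. In the limitations paragraph of the Discussion, the demanding measures are again discussed as study procedures. Inclusion criterion 3 points the other way, because it names procedures and assessments as two things. The literal reading is that assessment stops. At best the text is ambiguous.

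**3. What is left to impute from (Table 1)?**

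| Outcome | Measured | Left after an event just after week 4 |
|---|---|---|
| BDI-II | T0 and weekly to T7, then T8, T9 | T0 to T4 |
| MADRS | T0, T4, T7, T8, T9 | T0, T4 |
| M-CIDI | T0, T7, T8, T9 | T0 only |

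BDI-II at T7 is the best protected. MADRS and M-CIDI are more exposed, as are the 6-month outcomes that H2 also covers, because their earlier values are fewer or more distant.

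**4. How good is imputation from the weekly scores?** This is an illustrative simulation, and all inputs are assumed: random-intercept SD 0.7, slope SD 0.08 per week, residual SD 0.5, and an event after week 4 that is likelier with higher scores at weeks 3 and 4 (about 2.3% of patients). Week-7 scores were predicted by regression on weeks 0 to 4, fitted in those who stayed.

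| Event brings | True week-7 mean of excluded | Imputed | Mean of those who stayed |
|---|---|---|---|
| no further worsening | +0.71 SD | +0.71 SD | −0.02 SD |
| 1 unit of further worsening | +1.66 SD | +0.69 SD | −0.02 SD |

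In the first row imputation is unbiased. In the second it is too optimistic by 1.66 − 0.69 = 0.97 SD.

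**5. Size of the bias in the arm difference.** Bias = (p₁ − p₂) × δ, where p is the share excluded in each arm and δ is the shortfall of the imputed score in SD, taken as equal in both arms. The documents give neither, so both are assumptions.

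| p₁ vs p₂ | δ = 0.5 | δ = 1.0 | δ = 1.5 |
|---|---|---|---|
| 3% vs 3% | 0 | 0 | 0 |
| 5% vs 2% | 0.015 | 0.030 | 0.045 |
| 10% vs 5% | 0.025 | 0.050 | 0.075 |
| 10% vs 2% | 0.040 | 0.080 | 0.120 |

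With unequal rates the range is 0.015 to 0.12 SD. That is 0.015/0.36 = 4% to 0.12/0.36 = 33% of the margin, and 4% to 30% of d = 0.4.

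**6. Effect on the non-inferiority error.** With 100 per arm, the standard error of the difference is √(2/100) = 0.141 SD. If schema therapy is truly worse by exactly 0.36 and the bias b favours it, the chance of a false non-inferiority claim is 1 − Φ(1.645 − b/0.141). For b = 0.015 this is about 6%, and for b = 0.12 about 21%, against a nominal 5%.

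**7. Do these exits count as drop-outs?** Acute suicidality is itself an exclusion criterion, so the second drop-out group can cover it, although the example given there is a diagnosis that predates the trial. A suicide attempt is not named. For the third group, 4 sessions × 7 weeks = 28 are planned, and more than six means at least seven, or 7/4 = 1.75 weeks. If undelivered sessions count as missed, most earlier events qualify. An event in the last one to two weeks may not.

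**The case against.** The strongest reply has four parts.

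- **Excluded patients are not lost from the analysis.** Intention-to-treat with multiple imputation keeps them in their randomised arm, and their weekly BDI-II scores before exit are used. This stands. A reader might infer that they are filled in with average values, but the documents do not say so, and in step 4 they were imputed at about +0.7 SD rather than −0.02. What remains is the narrower case of worsening that earlier scores do not show.
- **Drop-out status.** A reader might infer that these exits are not counted as drop-outs. The text does not support that, because the second or third group may cover them. What remains is that the classification is unclear.
- **The size is modest and assumed.** Every non-zero row in step 5 assumes a two- to five-fold difference in rates. Acutely suicidal patients are excluded at entry, and all arms receive the same hospital setting with unrestricted medication. Even 0.12 SD is below one standard error (0.141). This stands, so the documents do not show that a more harmful arm would win. The bias would matter mainly for a result close to a decision boundary.
- **The imputation model and sensitivity analyses usually sit in the analysis plan, which is not shown.** This also stands, and their absence is not the finding. The finding is a rule the article does state. An analysis plan can soften its effect but cannot supply scores that were never collected.

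**Conclusion.** The concern holds in a limited form. As written, the rule ends outcome measurement after an event tied to the outcome. This undercuts the stated intention-to-treat approach and creates avoidable missing data, probably not at random. The bias is zero if exclusion rates and shortfall are equal across arms, or if earlier scores fully predict the later ones. Otherwise it is roughly 0.015 to 0.12 SD under the assumed rates and shortfalls, in favour of the arm with more such events. BDI-II at week 7 is the least affected. MADRS, M-CIDI and the 6-month outcomes are more so. Whether these exits belong to the drop-out outcome is unclear rather than settled either way. The literal reading of the rule is well supported, but the size rests wholly on assumptions.

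**What to change.** Reconcile the adverse-event rule, the missing-data paragraph and the drop-out definition.

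- Separate exclusion from study treatment and optional measures from outcome assessment. Unless consent is withdrawn, keep collecting at least the BDI-II at T7, T8 and T9, online where needed (online questionnaires are already used at follow-up), and blinded MADRS and M-CIDI ratings where feasible.
- State that these exits count in the drop-out outcome, naming both acute suicidality and suicide attempt and whatever the week in which they occur.
- Add a sensitivity analysis in which imputed values for these participants are shifted worse by fixed amounts, for example the 0.5 to 1.5 SD used above, and report the number of such exits per arm.

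The cost is a short amendment and a few extra questionnaires for a small number of participants. Randomisation began in September 2017, so assessments already missed for excluded participants cannot be recovered, and the sensitivity analysis must carry those cases. The proposal concerns data collection only. The clinical handling of these events is left as it is, and no view is given on it.

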## Discussion

The acute and sustainable treatment of MDD is one of the most urgent health related challenges of our times, as it constitutes one of the leading causes of disability and disease burden today and in the future [197]. Comorbidities on axis I and II are associated with mood disorders [198] and play a key role as risk factor for recurrence of MDD [199]. Originally developed for non-responders of cognitive therapy and effective in the treating of PD [15, 33], ST represents a promising approach in the treatment of psychiatric disorders in general and MDD in particular. It focuses on the modification of trait-like EMS which play a key role in the development and maintenance of psychopathology. Therefore, ST is tested in the current trial in an inpatient and day clinic setting as a psychotherapy approach for MDD in its rather severe manifestations characterized by recurrence, comorbidities especially on axis II, and chronical courses.

The OPTIMA-Trial overcomes several short-comings of prior research projects on the effectiveness of ST. The design of the study combines external validity of a naturalistic inpatient and day clinic setting with methodological standards of clinical trials such as randomization procedure, allocation concealment, blinding of outcome assessments, adherence ratings and by conducting intention-to-treat analysis. Additionally, the study implements recommendations for psychotherapy RCTs [103] e.g., by applying treatments to a rather heterogeneous sample (e.g., with respect to age range and comorbidities), using an active control arm (IST), adding behavioral and biological markers, combining self-assessments and clinical assessments (M-CIDI or MADRS) as outcome variables, and following standardized/manualized psychotherapy protocols. Beyond this, we added two follow-up visits after study completion (at month 6 and 24) to gain insight into long-term effects of our interventions that are both clinically and economically relevant.

Nevertheless, this study faces some challenges and has methodological limitations. First, it is in the nature of psychotherapy trials, that the blinding of participants and personnel (except from raters) is impossible to achieve. Thus, therapy expectancy effects constitute a potential risk of bias [200]. Second, the study duration of 7 weeks could be judged as too short to capture lasting treatment effects of psychotherapy. Specifically, one might expect a greater impact of psychotherapy when it is administered for a longer period of time. Yet, considering the inpatient and day clinic sample of the trial, 7 weeks displays a realistic picture of the clinical reality rather than a longer stay at the hospital. To account for the short treatment phase, we plan two later assessments at 6 and 24 months post-treatment to cover these long-term effects. Third, from a pure methodological perspective, a “psychopharmacotherapy only” and/or a “psychopharmacotherapy free” treatment arm would enable us to detect the relative contributions of ST and ADM to the recovery more accurately. However, the combination of ADM and psychotherapy is considered as gold standard in the treatment guidelines of MDD [93]. Given that the participants in our sample suffer from rather severe forms of MDD at the time point when they are being enrolled in the study, we decided not to include a “psychotherapy only” or “psychopharmacotherapy only” arm in the study design for ethical reasons. Fourth, the semi-open structure of the group sessions means varying patient constellations and potential therapist change, which might disrupt therapy processes and the development of therapy alliance and group cohesion. Fifth, the measures in the current research are time consuming and demanding. Loss of motivation is a core feature of depression and therefore, the study procedures might bias the selection of participants and facilitate drop outs. Even though, we cannot totally rule out this limitation, we hope to lower such biases by reducing the obligatory measurements to a minimum and adapting measurement procedures to the participants’ schedule to make participation as convenient as possible. Beyond that, we will use CONSORT guidelines [201] to ensure a transparent reporting of the trial and detect and evaluate potential remaining sampling biases when interpreting results in terms of generalizability. Since the major parts of the measurements happen before and after treatment, we do not consider them to interfere with the process of psychotherapy. Sixth, psychotherapy is one element of comprehensive inpatient and day clinic treatment approach including ADM and further elements of psychiatric care. Nevertheless, as outlined above, we assume psychotherapy and specific intervention techniques like in ST to play a major role in the treatment of depression and therefore expect an additional effect to non-specific therapy (IST). In accordance with treatment guidelines [101] and to assure psychotherapy not to be neglected in the overall care, we choose a relatively high treatment dose when comparing ST with CBT. In order to avoid biases in favor a non-inferiority hypothesis, we chose a rather small non-inferiority margin and will take this aspect into account when interpreting the results. Furthermore, all additional therapies and ADM will be documented and considered for later use in the statistical analysis as potential confounder. Even though we assume the further elements of psychiatric care to average out between arms, improvement in symptom severity cannot be directly associated to the specific psychotherapy interventions alone. The inclusion of psychotherapy in daily psychiatric care constitutes a methodological challenge, but simultaneously provides the opportunity to test treatment effects in a realistic scenario. Finally, pilot data suggests that the application of the mentioned inclusion and exclusion criteria will result in a sample consisting of partly moderate, but mainly severe forms of MDD. Such a sample represents reality in an inpatient and day clinical settings, but has to be taken into account as a factor when generalizing the results.

In conclusion, by its multimodal character, the broad inclusion criteria, and randomization into standardized psychotherapy treatment arms, the OPTIMA Trial addresses key questions on how psychotherapy in treatment of MDD can be optimized in a realistic clinical setting and helps to gain insights into a better understanding of predictors and mechanisms of different approaches of psychotherapy.

## Trial status

This is the first version of the protocol. First patient was randomized in September 2017. The recruitment phase of the trial will be completed by end of 2022 including follow-up measurements.

## Data Availability

Not applicable.

## Abbreviations

MDD: Major Depressive Disorder
ADM: Antidepressant Medication
ST: Schema Therapy
CBT: Cognitive Behavioral Therapy
PD: Personality Disorder(s)
EMS: Early Maladaptive Schemas
IST: Individual Supportive Therapy
MOCs: Mechanisms of Change
ECG: Electrocardiography
EMA: Ecological Momentary Assessment
BDI-II: Beck Depression Inventory-II
MADRS: Montgomery-Asberg Depression Ratings Scale
M-CIDI: Munich-Composite International Diagnostic Interview
BSI: Brief Symptom Inventory
WHODAS: World Health Organization Disability Assessment Schedule
WHOQOL: World Health Organization Quality of Life
HR: Heart Rate
RNT: Repetitive Negative Thinking
HRV: Heart Rate Variability
DNA: Deoxyribonucleic Acid
RNA: Ribonucleic Acid
EDTA: Ethylenediamine Tetra acetic Acid
PBMCs: Peripheral Blood Mononuclear Cells
DMSO: Dimethyl Sulfoxide
fMRI: Functional Magnetic Resonance Imaging
DTI: Diffusion Tensor Imaging
MCID: Minimal Clinically Important Difference
